## Abstract

**Objectives:**

To determine the preventive effects of supervised resistance training on arms volume, quality of life, physical performance, and handgrip strength in Chilean women at high risk for breast cancer-related lymphedema (BCRL) undergoing chemotherapy.

**Design:**

Randomized control trial.

**Participants:**

One hundred and six women at high risk for breast cancer-related lymphedema aged 18 to 70 years.

**Interventions:**

Participants will be randomized into two groups: [a] intervention, who will receive 12 weeks of supervised resistance training (STRONG-B) during adjuvant chemotherapy; and [b] control, who will receive education to promote lymphatic and venous return, maintain range of motion, and promote physical activity.

**Main Outcome Measures:**

The primary outcome will be arms volume measured with an optoelectric device (perometer NT1000). Secondary outcomes will be quality of life, handgrip strength, and physical performance. Primary and secondary outcomes will be measured at baseline, just after the intervention, and 3 and 6 months after. Statistical analysis will be performed following intention-to-treat and per-protocol approaches. The treatment effect will be calculated using linear mixed models.

**Discussion:**

The STRONG-B will be a tailored supervised resistance training that attempts to prevent or mitigate BCRL in a population that, due to both intrinsic and extrinsic factors, will commonly suffer from BCRL.

**Clinical Trial Registration:**

[https://clinicaltrials.gov/ct2/show/NCT04821609], identifier NCT04821609.

## Introduction

Breast cancer is the leading cause of cancer mortality among women worldwide (1–3). While early detection and better treatment strategies have improved overall survival (4, 5), patients often develop adverse effects such as fatigue, pain, sensory loss, impairments in shoulder range of motion and muscle strength, axillary web syndrome, and lymphedema (6–10). These effects ultimately impair survivors’ quality of life and physical performance (11–14).

Among the adverse effects, lymphedema deserves attention because of its chronic nature (15). One-third of breast cancer survivors develop breast cancer-related arm lymphedema (BCRL), 80% of them closely after treatments (16–18). BCRL is an excess accumulation of protein-rich fluid that would otherwise drain *via* the lymphatic system, leading to regional swelling in one or both arms after breast cancer (19, 20). BCRL has multifactorial causes, influenced by treatment strategies and the patient’s ability to form collateral lymphatic pathways post-injury (20, 21). Major risk factors for BCRL are obesity (body mass index ≥30 kg/m^2^), extensive breast and axillary lymph node surgery, radiotherapy in lymph node basin, and taxane chemotherapy (10, 14, 20, 22). Clinically, BCRL is characterized by increased arm volume associated with pain, heaviness, tightness, and a decreased range of motion, thus impacting the quality of life (23, 24).

The treatment for BCRL focuses on volume control through physiotherapy and compression garments (25–27), which represents a high economic burden for patients and the health care system (28). Identifying strategies to prevent BCRL in individuals at high risk, and to improve quality of life of patients is necessary (27).

Historically, there has been objection to promoting physical exercise or weight lifting to breast cancer survivors (29). Nevertheless, this is currently regarded as safe (30). Indeed, there has been an emerging interest in physical exercise (aerobic and resistance) as a safe and effective complementary intervention to prevent or diminish the adverse effects related to breast cancer treatments (31–33).

Exercise increases cardiac output and arterial blood pressure, thus promoting capillary filtration and the entry of fluid and proteins into lymphatic capillaries (34). Exercise also increases lymph propulsion through lymphatic vessels through extrinsic and intrinsic mechanisms, e.g. skeletal muscle pump, respiratory pump, and the pulse of blood vessels near to lymphatic system (34–36). Indeed, lymphatic clearance rates during the initial 15 min of exercise are 5-fold higher than at rest, and remain elevated during exercise (~2.5-fold) (37). Further, physical activity has been shown to improve the quality of life in women with breast cancer (38–40). As mentioned above, physical activity has been also used safely to treat BCRL in survivors (33).

Recent systematic reviews suggest that resistance exercise is a potentially effective strategy to prevent BCRL in women (30, 41); however, few studies included women exclusively at high risk of BCRL (33, 42). The results reported may thus not apply to women at high risk of BCRL. In addition, the studies including women at high risk of BCRL used resistance training with light loads (33). Light training load has a small effect on muscle strength and morphological adaptations, and minor improvements in physical performance and quality of life (41). In contrast, acute (43) and cumulative (42) heavy-load resistance exercises improved the quality of life, muscle strength, and physical performance without increasing risk for BCRL.

Therefore, this study will aim to determine the preventive effects of supervised resistance training on arms volume, quality of life, physical performance, and handgrip strength in women undergoing adjuvant chemotherapy with a high risk of BCRL.

## Methods

### Study Design

This manuscript is a study protocol for a two-arm, randomized controlled trial (STRONG-B). The protocol adheres to the Recommendations for Interventional Trials (SPIRIT) guidelines (44) and the CONSORT statement (45) (**Figures 1**, **2**, respectively). The STRONG-B trial has been registered in Clinicaltrial.gov (code NCT04821609).

**Figure 1 f1:**
[figure not shown]
Schedule of enrolment, interventions, and assessments according to SPIRIT diagram.

**Figure 2 f2:**
[figure not shown]
The proposed CONSORT diagram of enrolment, allocation, follow-up, and analysis through the study for each arm.

The study population will be participants with breast cancer recruited from Complejo Asistencial [name] Río by medical referral. Recruitment will take place in two distinct phases. First, a nurse will identify potential participants, and the health and medical records of volunteers will be further analyzed in a multidisciplinary committee, including medical oncologists, surgeons, and radio-oncologists. In the second phase, each volunteer’s eligibility will be confirmed by an oncologist during medical consultation. The same nurse of the first recruitment phase will then explain to each potential volunteer the purpose of the study and perform the informed consent process. Reasons for withdrawal from the study will be recorded.

### Eligibility Criteria

The following inclusion criteria will be applied: [a] women between 18 and 70 years old; [b] diagnosis of primary breast carcinoma with histological confirmation; [c] total or partial mastectomy with axillary node dissection; [d] sentinel node biopsy with positive axillary web syndrome (defined as cord in the subcutaneous tissue from the axilla into the ipsilateral upper arm); [e] sentinel node biopsy along with a body mass index between 30.0 and 39.9 kg/m^2^; [f] indication of adjuvant chemotherapy; and [g] participants able to understand and respond to simple instructions. The exclusion criteria will be: [a] >200 ml of difference in volume between arms; [b] antineoplastic treatment (chemotherapy, radiation therapy, or hormone therapy) before the current medical diagnosis; [c] stage IV breast cancer; [d] medical contraindication for exercise; [e] self-reported physical activity equivalent to the recent American College of Sports Medicine Physical Exercise Recommendation Guidelines for Patients and Cancer Survivors: 150 min/week of moderate aerobic exercise, or 75 min/week of vigorous aerobic exercise, and resistance training exercises at least two days per week; [f] body mass index <18.5 kg/m^2^ (indicative of malnutrition) or >40 kg/m^2^ (indicative of high cardiovascular risk); and [g] pregnancy.

### Intervention

STRONG-B is an exercise training intervention specifically developed for patients with breast cancer (46), which follows the guidelines of the American College of Sports Medicine with the specification for the frequency, intensity, time, and type of exercise prescription (31).

The training sessions include ten moderate-intensity resistance exercises for the upper (shoulder press, chest press, lateral pulldown, biceps curls, triceps extension) and lower limbs (squat, calf raise, leg press, leg extension, and leg curl). Each session lasts ~40 minutes and will be conducted twice a week for 12 consecutive weeks. Sessions will be supervised and guided by experienced physiotherapists, and conducted in groups of up to 3 participants.

The training will begin the week after the first chemotherapy session and will be conducted concomitantly with the regular treatment of each patient. Note that STRONG-B will never replace or interfere with the standard care. Each session will include a warm-up (5 minutes), followed by resistance training (30 minutes), and ending with a cooldown (5 minutes).

Resistance exercises will be performed at the maximum range of motion, using resistance machines or free weights as required. Rating of perceived exertion will be measured using a 0–10-point OMNI-Resistance Exercise Scale (minimal effort = 0; maximum effort = 10) to control perceived exercise intensity (47, 48).

During the first week, patients will perform two sets of 10 repetitions of each exercise either without resistance or with the lowest resistance available for a rating of perceived exertion of 2–4 (“easy” to “somewhat easy”). After this week, provided that no adverse events or symptoms are reported, resistance will be added so that each patient can perform three sets of 12 maximal repetitions (12-Repetition maximum) of each exercise with a rating of perceived exertion of 4-6 (“somewhat easy” to “somewhat hard”) (47, 48).

Progression will be supervised considering the patient’s symptoms (49). When patients can complete three consecutive sessions with the last volume and intensity, the load will be increased 5% to 10%. During the 12th week, the number of steps per day will be recorded using a smart bracelet [Huawei Band 4 (50)] as a surrogate of aerobic physical activity.

### Control Group

Patients in the control group will be referred to an early and prospective physical therapy program, as previously described (51). Therein, they will be evaluated and educated, but this program will not include the STRONG-B training. In the first session (before surgery), patients will receive oral and written education. Education will consist of care advice and eight exercises (**Supplementary Data**) to promote lymphatic and venous return and to maintain arm range of motion. We will recommend patients to perform these exercises in 3 sets of 10 repetitions, 2-3 times a day, for 3 months after surgery. Patients will be also educated to encourage aerobic physical activity. Physical exercise will be evaluated and supervised every three months after surgery, and educational information will be reminded. During the 12th week, the number of steps per day will be recorded using a smart bracelet [Huawei Band 4 (50)] as a surrogate of aerobic physical activity.

## Outcomes

### Main Outcome

Arm lymphedema will be assessed using a Perometer (NT 1000, Wuppertal), an optoelectrical imaging device that measures limb volume (52). The perometer is a valid and reliable tool [interclass correlation coefficient test-retest of 0.99 (52)]. The volume is expressed in milliliters and percentage relative to the contralateral arm. A difference in volume between arms of 200 mL or higher and a 10% difference between arms indicate lymphedema (12).

### Secondary Outcomes

Quality of life will be assessed using two questionnaires: [a] the European Organization for Research and Treatment of Cancer Quality of Life Questionnaire Core 30 v.3.0 [EORTC QLQ-C30; test/retest reliability between 0.82 and 0.91 (53)]; and [b] the European Organization for Research and Treatment of Breast Cancer-Specific Quality of Life Questionnaire BR23 [EORTC QLQ-BR23; Cronbach’s α between 0.46 and 0.94 (54)]. These questionnaires had been validated in the Spanish language and Chilean population (55).

Handgrip strength will be measured with a Hydraulic Hand Dynamometer (Jamar, United Kingdom). Patients will be asked to grip and squeeze the dynamometer as hard as possible. The maneuver will be conducted three times, with 1-min rest between attempts. Both hands (with surgery, without surgery) will be measured and compared. Results will be expressed in kilograms. Intra-instrument reliability and concurrent validity were tested using certified standard weights (r = 1.00), while inter-instrument reliability was good, between 0.80 and 0.83 (56). Further, there are reference values for a healthy Chilean population (57, 58).

Physical performance and mobility will be assessed with the 6-minute walk test (59). The test has been validated in patients with cancer and shows good reliability [intraclass correlation coefficient for test/retest was r=0.93 (60)]. Participants will be instructed to walk between two marks set 30 m apart as many times as possible over 6 min. The greater the distance covered, the greater mobility and general performance (59). Results will be expressed in meters walked.

### Sociodemographic and Clinical Data

Demographic data will include age, sex, and educational level. Anthropometric data will include weight, height, and body mass index. Clinical data will include disease stage, scheduled treatment, medical history, and current medication. Clinical data will be extracted from the patients’ electronic medical files by one study coordinator not blinded to patient allocation.

### Safety and Feasibility

The safety of the intervention will be assessed every week, tracking and monitoring adverse events according to the National Cancer Institute Common Terminology Criteria for Adverse Events version 5.0 (61). Researchers will meet weekly to review and discuss adverse events. All serious adverse events will be immediately reported to both ethics committees and will be reported in the results.

The number of patients who meet the eligibility criteria, the number of patients who agree or not participate, and the number of patients who withdraw from the study will be recorded and reported. Adherence will be calculated considering the number of patients who participated in all sessions and the number of patients who assisted to scheduled assessments.

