### Statistical Analyses

Analyses will be performed by a statistician blinded to the allocation of patients. Intention-to-treat and per-protocol approaches will be used. Normality assumption will be tested using the Shapiro-Wilk test. If the normality assumption is met, data will be presented using means and standard deviations. Otherwise, median and interquartile ranges will be reported. To assess the effect of the intervention, a multivariate linear regression model with repeated measurements will be adjusted. The model will include arm volume, quality of life, physical performance, and handgrip strength as response variables. Group (intervention, control), time (t0, t1, t2, t3), and the group×time interaction will be included as explanatory variables, adjusted for co-variables if required. The intervention’s effect will be also described by computing the effect size and 95% confidence limits. The following qualitative descriptors will be used: trivial <0.20, small 0.20-0.50, moderate 0.50-0.80, and large >0.80 (62). Significance will be set at p<0.05. Statistical analyses will be performed with STATA 15.1.

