## Discussion

STRONG-B is a supervised resistance training intervention developed specifically for preventive BCRL in patients with breast cancer at high risk of BCRL. The training will be performed after breast cancer surgery and concomitantly with adjuvant chemotherapy. Considering the impact of cancer and the consequences of the treatments (6–14), the main objective will be to analyze the preventive effects of STRONG-B on arm volume, quality of life, physical performance, and handgrip strength. The feasibility, adherence, and security of the training will be also analyzed. STRONG-B is thus proposed as a tailored resistance training intervention supervised by experienced physiotherapists with multiple potential benefits for patients with breast cancer.

The economic burden of BCRL is high for patients and the health care system (28, 63–65). Three weeks of lymphatic decongestive treatment by a physiotherapist and follow-up require on average USD 2,648 per patient. Additionally, the required compression stockings cost on average USD 937 per patient (28). Finally, there are other non-medical costs such as transportation and loss of productivity due to morbidity and mortality. Together, these data highlight the relevance of developing strategies to prevent BCRL. Physical exercise may represent a plausible strategy (41, 66). If the STRONG-B training is successful, it would be easy to implement in usual care. Since resistance training is safe and well-tolerated in patients with breast cancer, the training may even be used as a primary prevention strategy against lymphedema and deterioration of quality of life.

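### Training adherence is counted from women who took part in all sessions, which with 24 planned sessions gives a figure that cannot be read back to attendance

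*Protocol article*

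**What the plan says.** The protocol article gives one rule for adherence, under Safety and Feasibility: "Adherence will be calculated considering the number of patients who participated in all sessions and the number of patients who assisted to scheduled assessments". Both parts are counts of patients, one for training sessions and one for assessment visits.

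The Intervention section sets the number of sessions: training "will be conducted twice a week for 12 consecutive weeks". The total of 24 is not printed but follows directly.

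The Discussion presents adherence as a result to be reported: "The feasibility, adherence, and security of the training will be also analyzed". It also lists fatigue or discomfort during chemotherapy as something that may lower adherence.

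No other part of the article gives a different adherence measure, such as sessions attended per woman, a percentage of planned sessions, or an attendance cut-off.

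**The concern.** A count of women who attended everything discards nearly all the information in the attendance record. One missed session out of 24 removes a woman from the count, and so do nineteen. Training runs alongside adjuvant chemotherapy and the authors themselves expect tolerability to reduce adherence. Occasional absences are therefore likely, and an all-or-none count is least informative in that setting.

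Two things are at stake, both in how feasibility is reported. First, a programme with high attendance could be reported as having poor adherence. Second, the figure depends on two quantities at once: how many sessions were missed, and whether the misses fell on a few women or were spread over many. A reader judging whether the programme could go into usual care needs the first quantity and cannot recover it from the count.

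**Working it through.** The article states no adherence or attendance figure, so there is none to reproduce. The check asks what the literal rule would report under assumed attendance.

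**Inputs from the article**
- Planned sessions per woman: 2 per week × 12 weeks = 24 (Intervention).
- Women in the intervention arm: 106 / 2 = 53 (Sample Size; 1:1 allocation under Randomization).

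**Assumed inputs**
- Mean attendance p: 90%, 95% or 98%, which is 24p = 21.6, 22.8 or 23.5 sessions.
- Within-woman correlation of absences r: 0 (independent), 0.1 or 0.3.

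**Formulas**
- Independent absences: P(24 of 24) = p^24.
- Clustered absences: beta-binomial with a = p(1−r)/r and b = (1−p)(1−r)/r, so P(24 of 24) = B(a+24, b) / B(a, b), where B is the beta function.

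**Worked cases**
- p = 0.90, r = 0: 0.90^24 = 0.080; × 53 = 4.2 women.
- p = 0.95, r = 0: 0.95^24 = 0.292; × 53 = 15.5 women.
- p = 0.90, r = 0.1: a = 8.1, b = 0.9, giving 0.288; × 53 = 15.3 women.
- p = 0.95, r = 0.3: a = 2.217, b = 0.117, giving 0.733; × 53 = 38.8 women.

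**Share of women attending all 24 sessions (expected number of 53)**

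| Mean attendance | r = 0 | r = 0.1 | r = 0.3 |
|---|---|---|---|
| 90% | 8.0% (4.2) | 28.8% (15.3) | 53.3% (28.3) |
| 95% | 29.2% (15.5) | 54.2% (28.7) | 73.3% (38.8) |
| 98% | 61.6% (32.6) | 78.4% (41.6) | 88.4% (46.8) |

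**Reading the table**
- Across a row, mean attendance is fixed and only the clustering changes, yet the reported figure moves from 8% to 53% at 90% attendance and from 29% to 73% at 95%.
- Along the diagonals, a reported 29% fits either 90% attendance with r = 0.1 or 95% with r = 0. A reported 53–54% fits either 90% with r = 0.3 or 95% with r = 0.1.
- A woman attending 23 of 24 has attended 23/24 = 95.8% of her sessions and is not counted.

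**Check on the replacement summary.** Where more than half of women attend every session, the expected median number attended is 24. That holds in six of the nine cells: 53.3%, 54.2%, 73.3%, 61.6%, 78.4% and 88.4%. At r = 0.3 the median is 24 at all three attendance levels. A median with range would therefore repeat much of the problem. The mean percentage of planned sessions attended equals p in every cell and does not depend on r.

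**The case against.** The wording is loose. It says adherence will be calculated by considering certain numbers, with no denominator, formula or cut-off, and the authors may have meant attendance across all the sessions. If so, the substance of the point falls and only the sentence needs correcting. The all-sessions count is nevertheless what the text says, and nothing else in the article points to another measure. Nor is this a detail left to a fuller document, since the article states the rule itself.

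The harm is also limited and recoverable. No feasibility threshold or stopping decision rests on the count, withdrawals are counted separately, and supervised sessions will produce attendance records that can be summarised properly later. This stands, and it is why the point is minor.

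Two stronger readings are tempting, and the article supports neither.

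- **That adherence should also capture the load received.** Loading after the first week is conditional ("provided that no adverse events or symptoms are reported, resistance will be added"), and later steps are guided by symptoms ("Progression will be supervised considering the patient’s symptoms"). Women with full attendance may therefore train at different loads. But a woman held back for symptoms is following the prescription, so an adherence count that ignores load is not wrong on that account. The article already prescribes and monitors load, and a condensed article may leave dose summaries to the full protocol. The Introduction's remark, "Light training load has a small effect on muscle strength and morphological adaptations", does not help either. Loading is set at each woman's own 12-repetition maximum, so taking fewer load steps from there is not shown to be light training in that sense.
- **That the per-protocol analysis is compromised.** The Statistical Analyses section says only "Intention-to-treat and per-protocol approaches will be used". It does not tie the per-protocol set to the all-sessions count.

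**Conclusion.** The point holds as a minor one. Taken literally, the stated rule makes training adherence an all-or-none count over 24 sessions. With assumed mean attendance of 90% to 95% and within-woman correlation of absences between 0 and 0.3, it could report anything from about 8% to 73%, and the result cannot be converted back to attendance.

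The size rests on those assumed inputs, because the article gives no attendance rate. Ambiguity between attendance levels is not an artefact of assuming independent absences; it arises because the amount of clustering is unknown. If attendance is close to complete the distortion shrinks, although even at 98% the count ranges from 62% to 88%.

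The effect is confined to a feasibility result. The primary outcome and the intention-to-treat comparison are unaffected.

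**What to change.** In Safety and Feasibility, define training adherence for each woman in the intervention group as sessions attended divided by the 24 planned. Report the mean percentage attended, which is total sessions attended over total sessions planned, together with its distribution across women. The number attending all sessions may be kept as a secondary description. The count of women attending scheduled assessments stays as it is.

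The cost is about one sentence in the protocol and slightly more reporting, using attendance data that supervised sessions already generate. No extra visit, measurement or participant is needed, and the training prescription does not change.
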